## **Introduction**

Antenatal corticosteroids (ACS), particularly, betamethasone is routinely administered to pregnant women at risk for preterm delivery because of a known decrease in risk of respiratory distress syndrome, intraventricular hemorrhage, necrotizing enterocolitis, neonatal intensive care unit (NICU) admissions and neonatal death (1-3). Nevertheless, ACS has been shown to induce maternal hyperglycemia (4-6). In one study, 95% and 77% of non-diabetic women had blood glucose  $\geq 140$  and  $\geq 160$  mg/dL, respectively, at least once during 48 hours following ACS administration. The highest average blood glucose level of 155 mg/dL occurred at 30 hours after administration of betamethasone and the mean maximum blood glucose reached  $171 \pm 19$  mg/dL (5). In another study least squares means of serum glucose was 146 and 162 mg/dL one and two days following ACS betamethasone (6). The indications for antihyperglycemic treatment during pregnancy are pre- and 2 hours post-prandial glucose values of 95 mg/dL and 120 mg/dL, respectively.

The mechanism for ACS-induced maternal hyperglycemia includes antagonizing and decreasing insulin synthesis as well as increasing gluconeogenesis (7). Maternal hyperglycemia contributes to the ACS-induced neonatal hypoglycemia (4;8); the elevation in maternal blood glucose causes higher cord blood glucose and C-peptide levels leading for fetal hyperinsulinemia at birth and consequent hypoglycemia in the early newborn period (9;10). The association between higher maternal serum glucose levels and cord blood C-peptide levels is linear and is demonstrated in all the population including women who are not considered as having gestational diabetes mellitus (10). ACS administration was also shown to cause neonatal hyperbilirubinemia (8).

Neonatal hypoglycemia, particularly in preterm infants, is a major concern which leads to serious short and long term complications. The short term complications include neurogenic symptoms (jitteriness/tremors, sweating, irritability, tachypnea and pallor) and neuroglycopenic symptoms (poor suck or poor feeding, weak or high-pitched cry, change in level of consciousness (lethargy, coma), seizures and hypotonia), apnea, bradycardia, cyanosis, and hypothermia (11). Additional concern is the need for NICU admission causing early separation of baby from his or her mother. Neonatal hypoglycemia results in neuroglycopenia at a time when metabolic activity

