| Screening and enrollment:                                                     | 99  |
| Pregnant women receiving betamethasone due to increased risk for preterm delivery    | 100 |
| from Emek medical center, Baruch Padeh medical center, Assuta Ashdod medical         | 101 |
| center, Ziv medical center and Galil medical center                                  | 102 |
| Inclusion criteria:                                                           | 103 |
| - Pregnant women receiving betamethasone from 24 to 36.5 gestational weeks           | 104 |
| - Before or within 24 hours following the first dose of betamethasone                | 105 |
| - ≥18 years old                                                                      | 106 |
| Exclusion criteria:                                                           | 107 |
| - Women with pre-gestational and gestational diabetes mellitus (GDM)                 | 108 |
| - Known allergic sensitivity to metformin                                            | 109 |
| - Known chronic heart failure                                                        | 110 |

|                                                                                                                                                                                                                                                                                                                                                                                                                                                                                                                                                                                                                                                                  |                                                      |

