| • Manufacturer: Teva Pharmaceutical Industries Ltd (metformin Teva, glucophage), Dexcel Ltd, Israel (glucomin). If additional metformin tablets from additional manufacturers become available, they will be accepted as well.      | 182
183
184
185
186 |
| • The Side effects may include - Taste disturbance, nausea, vomiting, diarrhea, abdominal pain, hypoglycemia, bloating/abdominal distention, constipation and lactic acidosis ( very rare).                                         | 187
188
189               |
| • Storage at room temperature                                                                                                                                                                                                       | 190                             |
| • Maximal acceptable dose during pregnancy: 3,000 mg/day (21)                                                                                                                                                                              | 191                             |
| This medication was used in a previous study to treat maternal hyperglycemia during pregnancy with high efficacy and safety profiles (17). It was also used in non-diabetic pregnant women without severe significant adverse events (18). | 192
193
194               |
| Study randomization                                                                                                                                                                                                          | 195                             |
| Randomization will be done by computerized software according to power calculation inside sealed envelopes (concealment of allocation). In this way the study will be unbiased.                                                            | 196
197
198
199        |
| Statistics                                                                                                                                                                                                                   | 200                             |
| Categorical variables will be compared using Chi-square test or Fisher's exact test.                                                                                                                                                       | 201                             |

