| Continuous variables will be compared via the Student's t-test or Mann–Whitney-U test.                                                                                                                                                     | 202
203                      |
| Sample size:                                                                                                                                                                                                                 | 204                             |
| We set two primary outcomes. Adjustment for multiplicity of the primary outcomes was made using the method described by Holm (22).                                                                                                         | 205
206                      |
| For the maternal outcome (mean maternal daily glucose value):                                                                                                                                                                              | 207                             |
| In order to demonstrate a mean difference of 5 mg% with 10 mg% standard deviation in the mean daily glucose charts 156 women will be required (two tailed                                                                                  | 208
209                      |

alpha=0.025,power of 80%). This assumption was chosen due to its clinical relevancy.

For the neonatal outcome from preterm deliveries (the rate of neonatal hypoglycemia in preterm deliveries):

In the study of Gyamfi-Bannerman et al (4), neonatal hypoglycemia following antenatal betamethasone and placebo were 24% versus 15%, respectively. In the same study around 16% of neonates were born at term and all neonates were older than 34 gestational age. We hypothesized that the rate of hypoglycemia will be higher in preterm neonates due to stronger effect of betamethasone administration but treatment with metformin will reduce the risk to the baseline. In order to show a reduction in preterm neonatal hypoglycemic from 40% in the control group to 15% in the metformin group, a sample size of 98 neonates will be required. In twins' pregnancy, each twin will be analyzed separately.

Recruitment will be done until completion of the sample size for both primary outcomes.

Since one third of the women are expected to deliver prematurely the estimated sample size+10% drop outs is: 323 women.

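### Both primary outcomes are tested without adjustment, although gestational age, timing relative to betamethasone and centre are known at randomisation: the tests are valid, but precision is given away

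*Protocol*

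**What the plan says.** The Statistics section of the protocol gives one sentence for each type of variable: "Categorical variables will be compared using Chi-square test or Fisher's exact test" and "Continuous variables will be compared via the" t-test or the Mann–Whitney test. These are the only analyses stated for the two primary outcomes, mean maternal daily glucose and neonatal hypoglycaemia in preterm deliveries. There is no model, covariate or centre term. The Study randomization section describes computer-generated allocation in sealed envelopes and names no stratification factor.

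The population is broad. The inclusion criteria admit "Pregnant women receiving betamethasone from 24 to 36.5 gestational weeks", and enrolment may take place before the first dose or up to 24 hours after it. Five centres take part. The Introduction cites a study in which the highest average maternal glucose "occurred at 30 hours after administration of betamethasone".

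The Sample size section plans the maternal comparison on "a mean difference of 5 mg% with 10 mg% standard deviation", with two-tailed "alpha=0.025,power of 80"%, giving 156 women. The neonatal comparison is 40% against 15%, giving 98 neonates. Recruitment continues until both sizes are reached, and the stated total is 323 women.

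**The concern.** Under the Follow-up protocol, the glucose chart starts at enrolment. A woman enrolled before her first dose and one enrolled 24 hours after it therefore average different stretches of the glucose response to betamethasone. On the protocol's own evidence that response varies with time since the dose, so part of the between-woman variance probably reflects entry time. A two-sample test leaves that variance in the standard error.

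For the neonatal outcome, entry spans more than 12 weeks of gestation. If gestational age at randomisation predicts hypoglycaemia, an unadjusted comparison of about 49 neonates per arm does not use that information. Stratified randomisation would have recovered some of it, but none is stated.

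What is at stake is efficiency: wider intervals than necessary on both outcomes, and some lost power on the neonatal outcome, which drives the total sample size.

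**Working it through.** **Inputs from the protocol.** Maternal: difference 5, SD 10, two-sided alpha 0.025, power 80%, 156 women. Neonatal: 40% vs 15%, 98 neonates. One third of women deliver preterm, 10% drop out, total 323. Equal allocation is assumed because no ratio is stated.

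**Inputs assumed.** The protocol does not give the prognostic strength of the covariates. Ranges used: R² 0.1 to 0.3 (maternal) and odds ratio 1.5 to 3 per SD of one baseline covariate (neonatal).

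**1. The plan's figures come from unadjusted formulas.**
- Maternal, normal approximation: n per arm = 2 × (2.241 + 0.842)² × 10² / 5² = 76.04, so 77 per arm or 154 in total. With the noncentral t, 78 per arm (156) gives 80.4% power.
- Neonatal, pooled-variance formula at two-sided alpha 0.05: 48.9, so 49 per arm or 98. Power is 80.1%. The protocol does not restate alpha for this outcome; 0.05 is the value that reproduces 98.
- Total: 98 × 3 = 294 women; 294 × 1.10 = 323.4, i.e. 323.

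**2. Maternal outcome at the number the trial expects.** The neonatal target governs recruitment, so about 294 women (147 per arm) should be evaluable. Adjustment multiplies the residual SD by √(1 − R²). Unadjusted SE = 10 × √(2/147) = 1.166. Noncentral t, alpha 0.025:

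| R² (assumed) | SE | SE reduction | Power |
|---|---|---|---|
| 0 | 1.166 | – | 97.9% |
| 0.1 | 1.107 | 5.1% | 98.8% |
| 0.2 | 1.043 | 10.6% | 99.4% |
| 0.3 | 0.976 | 16.3% | 99.8% |

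If twins mean that fewer women are needed to reach 98 neonates, power is still high: at 130 per arm the unadjusted figure is 96.2%.

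**3. Neonatal outcome.** Simulation with 49 per arm, marginal risks held at 40% and 15%, one normally distributed baseline covariate and 3,000 trials per setting. It compares the unadjusted chi-square test with the likelihood-ratio test from a logistic model, at alpha 0.05:

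| Odds ratio per SD (assumed) | Unadjusted power | Adjusted power | Gain (points) |
|---|---|---|---|
| 1 (no prognostic value) | 80.5% | 81.1% | 0.6 |
| 1.5 | 80.7% | 82.2% | 1.5 |
| 2 | 80.6% | 83.4% | 2.8 |
| 3 | 80.1% | 87.2% | 7.1 |

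The first row shows that about half a point comes from the change of test and not from the covariate. The simulation treats neonates as independent, so it ignores twin pairs.

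**4. Validity.** With no treatment effect, the unadjusted test rejected in 4.7–5.3% of simulated trials and the adjusted test in 4.8–5.6%. Chance imbalance is not rare: the standardised difference in a baseline covariate has SD 2/√98 = 0.20, so it exceeds 0.25 SD in either direction in 22% of trials. The unadjusted test's error rate already allows for this.

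**The case against.** The strongest reply is that nothing here is an error. The two-sample tests are valid under randomisation, both sample sizes were set for them, and covariate choice is often left to a statistical analysis plan, which is not shown here. Most of this stands, and it limits the point to an efficiency improvement. It does not remove the point, because the protocol states its tests and derives its sample sizes from them. A later plan that used a model would be changing a stated method, and in an open-label trial that is best settled early.

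A reader might also infer more than the documents support:
- **That maternal power rises from 80% to 85–93%.** This holds only at 156 women. Recruitment continues to the neonatal target, and the Criteria for study removal keep women with data on either primary outcome, so the relevant number is about 294. The power gain there is 1–2 points.
- **That chance imbalance could make the neonatal result invalid.** It adds noise, which the test's error rate already covers.
- **That the protocol says hypoglycaemia risk rises with prematurity among preterm infants.** The Sample size section only hypothesises a higher rate in preterm neonates than in a cited cohort, all older than 34 weeks and about 16% born at term. It gives no gradient within the preterm range.

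Two practical objections also stand. Hours since the first dose is undefined for women enrolled before dosing, so the covariate needs a category for them. Gestational age at randomisation is only indirectly linked to gestational age at birth, so its prognostic strength may lie at the low end of the assumed range.

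**Conclusion.** The point holds as a loss of precision. The protocol fixes unadjusted tests for both primary outcomes and names no stratification factor, although gestational age and timing relative to the first dose must be known to apply the inclusion criteria, and centre is always known.

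Planned power is not undercut. The neonatal gain is modest, and the maternal gain is almost entirely in interval width. These sizes rest on assumed prognostic strength, equal allocation, the stated SD of 10, about 294 evaluable women, and alpha 0.05 for the neonatal outcome. If the covariates predict little, the gain is close to nil, and adjusting for a few prespecified baseline factors costs very little.

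**What to change.** Prespecify as the primary analyses:
- **Maternal glucose:** a linear model with arm, gestational age at randomisation, timing of randomisation relative to the first betamethasone dose (coded as not yet dosed, or hours since the dose), singleton/twin, and centre.
- **Neonatal hypoglycaemia:** a model that accounts for clustering within mother, with arm, gestational age at randomisation and singleton/twin. Include centre only if numbers allow. Report a standardised risk difference and risk ratio. Do not adjust for gestational age at delivery, which arises after randomisation.

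Keep the chi-square/Fisher and t/Mann–Whitney tests as sensitivity analyses.

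The cost is a change of wording in the Statistics section, made before outcome data are compared by arm. No extra participants, visits or measurements are needed. The times of the first dose and of randomisation should be named explicitly as recorded items: eligibility depends on them, but the Follow-up protocol's list of collected data does not mention them.

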| 2. Control group will not receive treatment with metformin.                                                                                                                                                                                                                                                                                                                                                                                                                                                                                                                                                                                                      | 130
131                                           |
| Follow-up protocol                                                                                                                                                                                                                                                                                                                                                                                                                                                                                                                                                                                                                                        | 132                                                  |
| Pregnant women that are at increased risk for preterm delivery will receive intramuscular (IM) injection of 12 mg betamethasone (celestone) according to physician's discretion. If delivery does not occur, additional IM 12 mg betamethasone injection will be administered 24 hours following the first injection as accepted (women that will not receive the second injection will not be removed from the study and metformin will be administrated). Before or within 24 hours from the first betamethasone injection the women will be enrolled to the study and will be allocated randomly to either the research or control groups as described above. | 133
134
135
136
137
138
139
140 |

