| Primary outcome:                                                                                                                                                                                                                                                                                                                                                                                                                                                                                                                                                                                                                                      | 162 |
| 1. Mean maternal daily glucose values                                                                                                                                                                                                                                                                                                                                                                                                                                                                                                                                                                                                                        | 163 |
| 2. The rate of neonatal hypoglycemia in preterm deliveries (<37 gestational weeks)                                                                                                                                                                                                                                                                                                                                                                                                                                                                                                                                                                           | 164 |

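### Twins count as separate neonates in tests that assume independence, although mothers are randomised; the standard error of the neonatal co-primary outcome is then too small

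*Protocol*

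**What the plan says.** - **Unit of randomisation.** Under Follow-up protocol, "the women will be enrolled to the study and will be allocated randomly to either the research or control groups". Both twins of a pregnancy are therefore always in the same arm. Multiple pregnancy is not among the exclusion criteria.
- **Outcome.** The second of the two primary outcomes is "The rate of neonatal hypoglycemia in preterm deliveries (<37 gestational weeks").
- **Unit of analysis.** The Sample size section assumes a fall "from 40% in the control group to 15% in the metformin group", says that "a sample size of 98 neonates will be required", and adds that in a twin pregnancy "each twin will be analyzed separately".
- **Test.** The Statistics section says: "Categorical variables will be compared using Chi-square test or Fisher's exact test". For continuous variables it names Student's t-test or the Mann–Whitney test. The protocol mentions no clustered model, robust variance, design effect or one-infant-per-mother rule.
- **Error rate.** Holm's method covers the two primary outcomes. The stated "alpha=0.025,power of 80"% belongs to the maternal calculation; the neonatal calculation states neither alpha nor power.

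**The concern.** Twins share the allocation, the mother's glucose, the timing of betamethasone and the gestational age at birth. The Introduction's own causal pathway runs from maternal glucose to neonatal hypoglycaemia, so a positive correlation within pairs is the natural expectation. A test that treats the two infants as unrelated counts more information than the trial holds. Its standard error is too small and its interval too narrow.

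This affects a co-primary outcome, and Holm's procedure controls the familywise error only if each p-value entering it is valid. The per-neonate secondary outcomes have the same fault. The protocol applies multiplicity control only to the primary outcomes, so for the secondary ones the consequence is intervals that are too narrow and nominal p-values that are too small.

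**Working it through.** **1. Reproduce the 98.** Inputs: 40% and 15% from the Sample size section; 1:1 allocation assumed, because no ratio is stated. For two independent proportions without continuity correction,

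n per arm = [z(α/2)·√(2·p̄·q̄) + z(β)·√(p₁q₁ + p₂q₂)]² / (p₁ − p₂)²

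with p̄ = 0.275, 2·p̄·q̄ = 0.39875 and p₁q₁ + p₂q₂ = 0.24 + 0.1275 = 0.3675. At two-sided 0.05 and 80% power: (1.960 × 0.6315 + 0.842 × 0.6062)² / 0.0625 = 48.9, so 49 per arm and **98 in all**. The figure reproduces with independent neonates and no allowance for clustering. (At two-sided 0.025 the same formula gives 60 per arm, 120 in all; that is a separate matter.)

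**2. Design effect.** Among n neonates in an arm, nf/2 pairs each add a covariance of 2·ICC·pq to the variance of the event count. The variance is npq + (nf/2)·2·ICC·pq = npq(1 + f·ICC). So DE = 1 + f·ICC, and the true standard error is √DE times the unadjusted one.

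**3. Type I error and power.** The actual chi-square error is 2·[1 − Φ(z_crit/√DE)], with z_crit 1.960 at 0.05 and 2.241 at 0.025. The power of an analysis that allows for clustering follows from step 1 with 49/DE per arm. f and ICC are assumptions; the protocol gives neither.

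| f | ICC | DE | SE factor | Error at 0.05 | Error at 0.025 | Effective neonates | Power at 0.05, cluster-adjusted |
|---|---|---|---|---|---|---|---|
| 0.1 | 0.2 | 1.02 | 1.01 | 5.2% | 2.6% | 96 | 79% |
| 0.2 | 0.5 | 1.10 | 1.05 | 6.2% | 3.3% | 89 | 76% |
| 0.3 | 0.5 | 1.15 | 1.07 | 6.8% | 3.7% | 85 | 74% |
| 0.4 | 0.5 | 1.20 | 1.10 | 7.4% | 4.1% | 82 | 72% |
| 0.5 | 0.7 | 1.35 | 1.16 | 9.2% | 5.4% | 73 | 67% |

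**4. Simulation of the two named tests.** 49 neonates per arm, a common event rate of 40%, 20,000 replicates:

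| f, ICC | Chi-square at 0.05 | Fisher at 0.05 | Chi-square at 0.025 | Fisher at 0.025 |
|---|---|---|---|---|
| no twins | 4.9% | 2.9% | 2.4% | 1.6% |
| 0.2, 0.5 | 6.3% | 3.9% | 3.3% | 2.2% |
| 0.3, 0.5 | 6.6% | 4.4% | 3.7% | 2.5% |
| 0.4, 0.5 | 7.2% | 4.7% | 4.0% | 2.8% |
| 0.4, 0.7 | 8.5% | 5.6% | 4.9% | 3.4% |
| 0.5, 0.7 | 9.2% | 6.2% | 5.3% | 3.6% |

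A repeat simulation put Fisher at 6.3% in the last case at 0.05. Chi-square agrees with the formula. Fisher starts well below nominal and passes 0.05 only with heavy twinning and high correlation; at the 0.025 step it passes nominal somewhat sooner.

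**5. Power of the unadjusted test.** Simulated power of the plain chi-square at 40% versus 15% is about 80% to 78% with twins, against 81% without. It barely moves, because that test goes on using a standard error that is too small.

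**The case against.** **The text fixes only a counting unit.** The twin sentence stands under Sample size, the list of tests is generic, and handling of correlated pairs is commonly left to an SAP, which is not at hand here. The word independent does not appear. This narrows the point but does not remove it. The protocol states the unit and names the tests, both tests assume independence, and the 98 reproduces without any clustering allowance. A clustered analysis in an SAP would have to depart from the tests named here.

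**The size is not in the document.** That is right. With few twins and weak correlation the chi-square error is about 5.2%, which is hardly a defect. The 9.2% needs half of the neonates to be twins and a correlation of 0.7. The protocol says nothing about how common twins will be.

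**Stronger readings that a reader might infer, and why they fail:**
- *Either named test breaches 5%.* Fisher's exact test stays below 0.05 in the low and middle cases. That protection is accidental, however, and the protocol leaves the choice between the tests open.
- *The planned test loses power, down to 67%.* The 79%–67% describes a valid, cluster-adjusted analysis. The unadjusted chi-square keeps about 80%–78%, at the price of its error rate.
- *The 0.05 figures always apply.* Under Holm the neonatal test reaches 0.05 only if the maternal outcome has the smaller p-value and is rejected first. Otherwise the 0.025 column applies.
- *More neonates must be enrolled.* Validity does not need this; it is a choice about power.

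**Conclusion.** The point holds in this limited form. Followed as written, the protocol gives a standard error on a co-primary outcome that is too small by √(1 + f·ICC), a factor of 1.01 to 1.16 over f 0.1–0.5 and ICC 0.2–0.7. If chi-square is used, the type I error is about 5.2%–9.2% at nominal 0.05 and 2.6%–5.4% at 0.025. If Fisher's test is used, the error still rises with twinning, but at 0.05 it exceeds nominal only with heavy twinning and high correlation.

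The conclusion rests on a positive within-pair correlation, on 1:1 allocation, and on ranges for f and ICC that are assumed. The direction is well supported by the protocol's own reasoning; the size is not known. The maternal primary outcome is not affected.

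**What to change.** Keep every neonate, and amend the Statistics section so that the neonatal primary outcome and the per-neonate secondary outcomes are analysed with the mother as the cluster. Suitable choices include GEE with a small-sample-corrected robust standard error, or a cluster-adjusted chi-square for the binary outcomes. Let the twin sentence under Sample size say that each twin contributes an outcome and that the analysis allows for the pairing.

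State beside the 98 the assumed twin share and correlation, and the resulting power: about 79%–67% at two-sided 0.05 over the range above, against 80% if all neonates were independent. Enrolling more is not required. If the sponsor chose to hold 80% at that level, 98 × DE gives 100 to 133 neonates over the same range.

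The change is one of wording. Eligibility, allocation, data collection and the outcome definition stay as they are. The price is slightly wider intervals and a slightly lower stated power.
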